
#### Additional Analysis to Characterize the Signals

Signals of potentially harmful DDIs that are supported by the aforementioned sensitivity and bias analyses will be further explored and characterized as follows:

Longer and shorter follow-up periods. To better understand the effects of prolonged medication exposure, we will extend the follow-up period beyond 30 days. We will rerun the regression analyses to examine the RRs and RDs for outcomes occurring within 60 and 90 days after cohort entry. We will also assess shorter follow-up periods by examining outcomes that occur within 7 and 14 days of cohort entry.Number needed to harm (NNH). To further quantify the absolute risk, we will calculate the NNH, which is derived from the RD (NNH=1/RD). This metric indicates how many patients would need to take the medication combination to result in harm to one additional patient who otherwise would not have been harmed. A lower NNH indicates a greater potential for harm [41].Population attributable fraction (PAF). We will calculate the PAF using the formula Pe(relative risk − 1)/[1 + Pe(relative risk − 1)], where Pe represents the proportion of the population exposed to the drug combination [42]. A PAF close to 1 suggests that eliminating the drug pair exposure could significantly reduce the number of adverse outcomes in the population, while a PAF close to 0 implies that reducing exposure would have minimal impact at the population level. Separate PAFs will be calculated for each outcome, and the results will be combined as a composite outcome before calculating the PAF for each cohort.

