**Results:**

In a preliminary analysis, we identified approximately 3.8 million older adults who filled prescriptions for over 500 unique medications during the study period (2002-2023), and therefore, approximately 200,000 potential drug combinations will be available for study. The initial drug pair cohorts had a median of 583 new users per cohort (IQR 237-2130); the median overlap in drug pair prescriptions was 57 days (IQR 30-90). The protocol was finalized on August 30, 2025, and outlines the analysis of data from 2002 to 2023. The analysis is scheduled to be completed by fall 2026, with results interpreted in 2027. The final manuscript submission is planned for December 2028.

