## Results

In a preliminary analysis, we identified approximately 3.8 million older adults who filled prescriptions for over 500 unique medications during the study period. Each drug can serve as drug A or drug B in various combinations, resulting in approximately 200,000 potential drug pairs for analysis. The initial drug pair cohorts had a median of 583 new users per cohort (IQR 237-2130), with a median overlap duration of 57 days (IQR 30-90). For example, in a chronic-chronic drug pair cohort where levothyroxine was drug A and rosuvastatin was drug B, the median overlap duration was 135 days among 128,762 patients, with 73.1% (n=94,036) females and a median age of 66 years. In a chronic-acute drug pair cohort (eg, levothyroxine as drug A and amoxicillin trihydrate as drug B), the median overlap was 10 days among 197,057 patients, with 74.8% (n=147,399) females and a median age of 67 years. In an acute-chronic drug pair cohort (eg, amoxicillin trihydrate as drug A and rosuvastatin as drug B), the median overlap was 10 days among 2702 patients, with 51.6% (n=1394) females and a median age of 66 years. Lastly, in an acute-acute drug pair cohort (eg, amoxicillin trihydrate as drug A and ciprofloxacin as drug B), the median overlap was 10 days among 4220 patients, with 59.4% (n=2507) females and a median age of 70 years. The protocol, finalized on August 30, 2025, outlines the analysis of data from 2002 to 2023. The high-throughput computing analysis is planned for completion by fall 2026, and findings from the analysis will be assessed in 2027 for clinical relevance by integrating PK, PD, and epidemiological evidence, supported by clinical validation tools. The final results will be prepared for dissemination, with manuscript submission planned for December 2028.

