### Challenges and Limitations

Despite using advanced statistical techniques to control for confounding, residual confounding may still be present [51]. Factors that are not captured in the administrative data or that are measured with error could bias our results [52]. To address this, we will conduct multiple sensitivity analyses and use negative control outcomes to assess the robustness of our findings [37].

Our study focuses on acute (30-day) outcomes, which will not capture the effect of long-term exposure [53]; however, we will conduct additional analyses to assess longer follow-up times.

The study is designed to identify harmful DDIs with a moderate-to-high risk in magnitude in cohorts of at least 1000 individuals, and therefore, it will have limited statistical power to detect small risk increases.

Our study does not include data on nonprescription (over-the-counter) drugs, drugs prescribed in hospitals, or comprehensive outpatient prescription drug use in children or adults aged under 65 years. These exclusions may limit the generalizability of our findings to a broader population. However, the focus on older adults is justified, given their higher risk of polypharmacy and adverse drug interactions.

Given the large number of comparisons being made, there is a risk of spurious findings due to multiple testing [16]. To mitigate this, we will apply the Benjamini-Hochberg procedure to control the false discovery rate and use E-values to assess the robustness of our findings against unmeasured confounding [31].

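### The 60- and 90-day reruns estimate risk after starting the pair, not the effect of prolonged exposure, except for pairs whose overlap covers the window

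*Protocol article*

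**What the plan says.** The section Additional Analysis to Characterize the Signals states the aim of the longer windows: "To better understand the effects of prolonged medication exposure, we will extend the follow-up period beyond 30 days". The method follows directly: "We will rerun the regression analyses to examine the RRs and RDs for outcomes occurring within 60 and 90 days after cohort entry". Nothing in that section ends follow-up when either drug runs out or restricts the analysis to patients still on both. The only censoring rule in the article is for death, in the 30-day Cox model under Sensitivity and Bias Analyses.

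Challenges and Limitations then relies on these reruns. It says that the study focuses on 30-day outcomes, "which will not capture the effect of long-term exposure [53]; however, we will conduct additional analyses to assess longer follow-up times".

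The Results section describes the initial drug pair cohorts "with a median overlap duration of 57 days (IQR 30-90"). Its four examples differ widely:

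- Chronic-chronic: "the median overlap duration was 135 days among 128,762 patients".
- Chronic-acute: "the median overlap was 10 days among 197,057 patients".
- Acute-chronic: "the median overlap was 10 days among 2702 patients".
- Acute-acute: also a median of 10 days, among 4220 patients.

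**The concern.** A longer follow-up window is longer exposure only if patients stay on both drugs. Exposed patients enter on the day drug B starts, so co-exposure runs from day 0. On the article's own figures, it will often finish before day 60 or day 90. The rerun then averages risk during co-exposure with risk after it. That is a legitimate quantity, the risk over a fixed period after starting the pair, but it is not the one named as the purpose.

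What is at stake is the interpretation of duration. If the RR falls between 30 and 90 days, the stated purpose invites the conclusion that harm fades with continued use, when stopping the combination could produce the same fall. A stable or rising RR cannot be credited to continued use either. The windows are also cumulative from day 0, so the 90-day result contains all the early events and does not isolate later risk.

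**Working it through.** **Inputs.** The overlap figures are from Results: median 57 days, IQR 30-90, with example medians of 135, 10, 10 and 10 days. The start of follow-up is from Cohort Entry Dates for Exposed and Referent Groups: the start of drug B. The windows are 30, 60 and 90 days. The overlap summary is descriptive and cannot be re-derived from the article.

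**Assumptions for the illustration (not from the article).** The rate ratio is 2 during overlap and 1 afterwards, with no carry-over. The baseline hazard is constant and events are rare.

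**Step 1: one overlap length.** For overlap L and window W, with L no longer than W, RR(W) = [2L + (W - L)] / W. If L exceeds W, RR = 2.

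| Overlap | 30 days | 60 days | 90 days |
|---|---|---|---|
| 57 days | 2.00 | (114 + 3)/60 = 1.95 | (114 + 33)/90 = 1.63 |
| 30 days | 2.00 | (60 + 30)/60 = 1.50 | (60 + 60)/90 = 1.33 |
| 10 days | (20 + 20)/30 = 1.33 | (20 + 50)/60 = 1.17 | (20 + 80)/90 = 1.11 |
| 135 days | 2.00 | 2.00 | 2.00 |

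The effect while on both drugs is the same in every cell. The falls come from time after overlap.

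**Step 2: a spread of overlap lengths.** Suppose the quartiles describe patients, so that the proportion still co-exposed is 1, 0.75, 0.50 and 0.25 at days 0, 30, 57 and 90. With linear interpolation, co-exposed time to day 90 is 30 × 0.875 + 27 × 0.625 + 33 × 0.375 = 55.5 days, and 55.5/90 = 62%. To day 60, with 0.477 still co-exposed at that day, it is 26.25 + 16.875 + 3 × 0.489 = 44.6 days, and 44.6/60 = 74%. Bounds come from letting overlaps end as early or as late as the quartiles allow.

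- 60 days: 26% of time is after overlap (14-39%), and RR = 1 + 0.74 = 1.74 (1.61-1.86).
- 90 days: 38% is after overlap (26-51%), and RR = 1.62 (1.49-1.74).
- Days 60 to 90 alone: co-exposed time is 55.5 - 44.6 = 10.9 of 30 days, so 64% is after overlap (50-75%).

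**Step 3: the alternative reading.** If the quartiles are taken across cohorts, about three quarters of cohorts have a typical overlap of 90 days or less. If that typical value is a median, about half or more of the exposed patients in those cohorts are off the pair by day 90.

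**Step 4: the chronic-chronic example.** With a median of 135 days, more than half are still co-exposed at day 90. If overlap were exponential, 2^(-90/135) = 63% would be. Co-exposed time would then be about 80% of the window, giving an RR of about 1.80.

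**The case against.** The strongest reply is that the reruns are done pair by pair, so a pooled overlap figure cannot condemn them all. This stands. A reader might infer that the 60- and 90-day results cannot show the effect of prolonged exposure for any pair. The article does not support that, because its chronic-chronic example has a median overlap beyond day 90.

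A reader might also take it as fact that half the patients have stopped by day 57 and three quarters by day 90. That is not established either. The sentence in Results also summarises new users per cohort, so the overlap quartiles may be across cohorts. They describe the initial cohorts, not those that will yield signals. The end of overlap is also not the end of all treatment, since a patient may continue one of the two drugs.

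The RR figures are illustrative. They assume that the excess risk stops on the last day of overlap, and carry-over would shrink the dilution.

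Two further points are fair. No signal is accepted or rejected on these reruns, because identification rests on the 30-day criteria and the sensitivity analyses. Risk over a fixed period after initiation is also a proper estimand. Multimedia Appendix 4, which summarises the additional analyses, is not shown and may say more. The point does not depend on that detail: the article itself states both a purpose and an analysis, and the analysis as described does not deliver the purpose for pairs with short overlap.

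**Conclusion.** The concern holds in a limited form. As written, the 60- and 90-day reruns estimate cumulative risk after starting the pair. They should not be described as effects of prolonged exposure, or offered as the answer to the long-term-exposure limitation, unless overlap in that pair covers the window. The mismatch is severe for pairs with an acute drug: at 10 days of overlap, only 10/90 = 11% of a 90-day window is co-exposed. It is intermediate near the reported median and smallest for chronic-chronic pairs. How many confirmed signals will be affected cannot be known from the article.

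The size rests on a rate ratio of 2, no carry-over, a constant baseline hazard and, for the population shares, reading the quartiles as describing patients. The direction of the dilution, towards the null when the excess risk ends with co-exposure, does not depend on the value of 2. The change is worth making before analysis. It affects how signals are characterised, not which signals are found.

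**What to change.** 1. In Additional Analysis to Characterize the Signals and in Challenges and Limitations, describe the 60- and 90-day reruns as risk after initiation of the pair.
2. For each confirmed signal, report the number of exposed patients still co-exposed at days 30, 60 and 90.
3. Base any statement about prolonged exposure on an added on-treatment Cox analysis. Censor exposed patients at the end of the A-B overlap plus a fixed grace period. Censor referents at the end of drug A supply plus the same grace period, or at a first fill of drug B. Use inverse-probability-of-censoring weights and report hazards by interval (0-30, 31-60 and 61-90 days), because a single hazard ratio averaged from day 0 would not isolate later exposure. Alternatively, limit such statements to pairs whose overlap covers the window.

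The cost is a few sentences of protocol text and one further automated analysis per confirmed signal. Fill dates and days' supply are already used to build the cohorts. The downsides are possible informative censoring, which the weights address only for measured factors, and sparse late data for pairs with an acute drug. The fixed-window result should therefore be kept alongside.

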#### Analysis to Balance the Exposed and Referent Groups in Each Cohort

Propensity scores will be calculated using multivariable logistic regression, incorporating more than 400 baseline characteristics (the complete list and coding definitions are provided in Multimedia Appendix 2). Characteristics include calendar year, prior use of drug A, demographics (eg, age, sex, neighborhood income quintile, urban vs rural residence, geographic region [31], and long-term care home residency), comorbidities (eg, asthma, diabetes, coronary artery disease) assessed over the 5 years before cohort entry, health care use in the year prior (eg, hospitalizations, emergency room visits, specialist consultations), and prescription drug dispensing within 120 days before cohort entry. The 120-day lookback period accounts for potential delays in prescription refills, ensuring comprehensive capture of medication dispensing.

The propensity scores will estimate the probability of a patient being in the exposed group versus the referent group, given their baseline characteristics. To enhance the comparability of the exposed and referent groups, we will exclude (1) individuals in the referent group with propensity scores lower than the lowest 1% of scores in the exposed group and (2) individuals in the exposed group with propensity scores higher than the highest 99% of scores in the referent group. This will also ensure that we do not violate the positivity assumption in causal inference, which requires that there should be a nonnull probability across each stratum of baseline characteristics within both the exposed and referent groups [32].

Inverse probability of treatment weighting (IPTW) using average treatment-effect-in-the-treated (ATT) weights will then be used to balance the exposed and referent groups on baseline characteristics as follows: Individuals in the referent group will be weighted using ATT weights, defined as their odds of being in the exposed group (propensity score/[1 − propensity score]). Individuals in the exposed group (the medication pair group) will receive weights of 1. This method will produce a weighted pseudosample of individuals in the referent group with a distribution of measured characteristics similar to that of the exposed group [33,34]. Between-group differences in baseline characteristics in the weighted samples will be examined using standardized differences (SDs) [35].

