#### Regression Analyses

A visual summary of the regression and additional exploratory analyses is provided in Multimedia Appendix 4. In each cohort, outcomes will be eligible for analysis if there are at least six outcome events in both the exposed and referent groups. Reporting fewer than six events could lead to potential patient reidentification and substantial estimation errors.

For each eligible cohort, we will use a modified Poisson regression model [36] to estimate the weighted risk ratio (RR) and its 95% CI for each outcome in the exposed group compared to the referent group. Additionally, a binomial regression model with an identity link function will be used to estimate the weighted risk difference (RD) and its 95% CI. If all 74 outcomes for a particular cohort are eligible, up to 74 regression models will be run.

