#### Criteria for Identifying Potential Signals of Harmful DDIs

Associations between a drug pair and an adverse outcome that meet the following criteria will be considered potential signals of harm and analyzed further:

Thresholds for RRs and RDs. The lower bound of the 95% CI for the RR must be ≥1.33, and for the RD, it must be ≥0.1%. These thresholds were chosen to ensure that only clinically significant increases in risk (of sufficient magnitude to be of concern) are considered. This analysis will focus solely on potential harms from drug combinations rather than protective benefits.Statistical significance. The *P* values from the modified Poisson regression model (for RRs) and the binomial regression model (for RDs) must be statistically significant after applying the Benjamini-Hochberg correction. This correction accounts for multiple comparisons across all outcomes and drug pair cohorts. The false discovery rate will be set at 5%, and the highest *P* value below the Benjamini-Hochberg critical value will be considered statistically significant, along with all *P* values below it. This correction will minimize the risk of false-positive discoveries (type I errors).

Drug pair cohorts that do not generate significant signals will not undergo further analysis.

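### The population attributable fraction uses a formula that is exact only without confounding, yet every risk ratio the plan produces is confounder-adjusted

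*Protocol article*

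**What the plan says.** The PAF is one of the measures planned for signals that survive the sensitivity and bias analyses (Additional Analysis to Characterize the Signals). The formula is fixed in the text: "We will calculate the PAF using the formula Pe(relative risk − 1)/[1 + Pe(relative risk − 1", with both brackets then closed, "where Pe represents the proportion of the population exposed to the drug combination". The section reads a value near 1 as a large potential reduction in adverse outcomes if exposure to the pair were eliminated, and a value near 0 as minimal population impact. It says only relative risk, without naming which one. It ends by referring to a PAF for each cohort.

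The RRs available come from Regression Analyses: "we will use a modified Poisson regression model [36] to estimate the weighted risk ratio (RR) and its 95% CI". The weighting is described under Analysis to Balance the Exposed and Referent Groups in Each Cohort: "Individuals in the referent group will be weighted using ATT weights, defined as their odds of being in the exposed group", while exposed individuals have weight 1. In the same section, "Propensity scores will be calculated using multivariable logistic regression, incorporating more than 400 baseline characteristics". The only other RR is from the 1:1 propensity-matched sensitivity analysis. No crude RR is planned.

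**The concern.** The formula compares the observed population risk with a counterfactual in which everyone has the risk of the unexposed. It therefore needs the unexposed risk to be what the exposed would have had without drug B. A study that adjusts for more than 400 characteristics does not expect this to hold. Entering an adjusted RR corrects the contrast but leaves the denominator wrong, because the referents' actual event rate no longer appears in it.

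At stake is the figure offered as the share of adverse outcomes that eliminating the pair would prevent. The direction of the error depends on who receives drug B. The PAF is understated when exposed people have the higher baseline risk and overstated when they have the lower. Because c can differ by pair and outcome, the error is not a constant factor that a reader could allow for.

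**Working it through.** The protocol states no numeric PAF, so there is no figure to reproduce. The check is algebraic, followed by illustrations.

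**Inputs from the document.** The formula, the weighted RR and the ATT weights are as cited above. For the size of RR, "The lower bound of the 95% CI for the RR must be ≥1.33", so point estimates for signals lie above 1.33. The Results give about 3.8 million older adults, a median of 583 new users per cohort, and one example cohort of 128,762 patients.

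**Assumptions.** c from 0.67 to 2; RR 2; Pe 10% and 30% as round values. Two further Pe values use the Results counts over 3.8 million: 583/3,800,000 = 0.015%, and 128,762/3,800,000 = 3.4% (if all are counted as exposed).

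**Notation.** R1 is the risk in the exposed, R10 the ATT-weighted referent risk, and R0 the crude referent risk. RR = R1/R10 and c = R10/R0, so the crude RR is R1/R0 = c × RR.

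1. True PAF. Avoidable events per person are Pe(R1 − R10), and all events per person are Pe·R1 + (1 − Pe)R0. Dividing by R0 gives PAF = Pe·c(RR − 1)/[Pe·c·RR + 1 − Pe].
2. Plan's formula with the weighted RR: Pe(RR − 1)/[1 + Pe(RR − 1)]. This is step 1 with c set to 1.
3. Ratio of plan to truth: [Pe·c·RR + 1 − Pe]/{c[1 + Pe(RR − 1)]}. As Pe approaches 0 it tends to 1/c: 1.49 at c = 0.67 and 0.50 at c = 2.
4. Case-based formula. Pc = Pe·c·RR/[Pe·c·RR + 1 − Pe]. Multiplying by (RR − 1)/RR gives step 1 exactly, for any c.

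**Worked example (Pe 10%, RR 2, c 1.5).**

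- True: 0.10 × 1.5 × 1/(0.10 × 1.5 × 2 + 0.90) = 0.15/1.20 = 12.5%.
- Plan's formula, weighted RR: 0.10/1.10 = 9.1%.
- Plan's formula, crude RR of 3: 0.20/1.20 = 16.7%.
- Case-based: Pc = 0.30/1.20 = 0.25, and 0.25 × 1/2 = 12.5%.

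**Range at RR 2.**

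| Pe | Plan's formula | True, c 0.67 | True, c 1 | True, c 1.5 | True, c 2 |
|---|---|---|---|---|---|
| 0.015% | 0.0153% | 0.0103% | 0.0153% | 0.0230% | 0.0307% |
| 3.4% | 3.28% | 2.24% | 3.28% | 4.76% | 6.15% |
| 10% | 9.1% | 6.5% | 9.1% | 12.5% | 15.4% |
| 30% | 23.1% | 18.2% | 23.1% | 28.1% | 31.6% |

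At an RR of 1.33, Pe 10% and c 1.5, the plan's formula gives 3.2% and the true value is 4.5%.

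**The case against.** The strongest reply is that little hangs on this number. The PAF is calculated only after a signal has been identified and supported. Signals are selected on RR, risk difference, false discovery rate and the bias analyses, and classified on external evidence; Table 2 does not use the PAF. The number needed to harm beside it comes from the weighted risk difference and does not share the fault. For a typical pair measured against all older adults, plan and truth are both close to zero (0.015% against 0.03% at c = 2). All of this stands, and it limits the point to a descriptive measure.

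It may also be said that the section does not say the weighted RR goes in. That is an inference, but no unadjusted RR is planned.

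Three stronger readings are tempting and not supported:

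- A reader might infer that the formula is right for a crude RR. It is not: under confounding the crude RR gives 16.7% against 12.5% in the example.
- A reader might infer that Pe is taken over all older adults, so that it does not match a referent group of drug A users. The section does not name the population, and its reference to a PAF for each cohort fits a population of drug A users equally well. The population is unspecified, not shown to be mismatched.
- A reader might infer that drug pairs will be misranked. No section ranks pairs by PAF; the visualization tool only lets users filter on RRs or other metrics and sort the data.

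Finally, exposed case counts for all regular users of drug A cannot be read directly from the cohort tables, because both groups are trimmed on the propensity score. That stands too, and the fix is limited to the trimmed cohort for this reason.

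**Conclusion.** The formula as written is wrong for the RRs this plan will produce. It is exact only at c = 1, where weighted and crude referent risks agree. Over the assumed range of c from 0.67 to 2, it runs from about 1.5-fold too high to 2-fold too low at small Pe. The relative error shrinks as Pe rises: at Pe 30% and RR 2, from 1.27-fold too high to 0.73 of the true value. That the formula is inexact under confounding follows from algebra and needs no assumption. The size and direction rest on c, Pe and RR values that the document does not give. The absolute error is very small for rare pairs and reaches several percentage points when Pe is 10% or more. The consequence is confined to the stated population impact of a signal; detection, error control and classification are unaffected.

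**What to change.** Replace the formula with PAF = Pc(RR − 1)/RR, where RR is the ATT-weighted RR and Pc is the proportion of cases that are exposed. Count Pc without weights, in the same propensity-trimmed cohort of regular drug A users that yields the RR. Weighted referent counts would bring the weighted risk back into the denominator. State that this cohort is the population to which the PAF refers.

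The cost is one changed formula and one added sentence. Event counts by group are already needed for the rule of at least six events in each group, but they must be taken after trimming. The small downside is that the PAF then describes the trimmed cohort and not all older adults, so the text on population-level impact should say so.
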